#### **5.1.3.5. Process if the trial is suspended on the basis of safety reports on first 40 subjects to receive each of the first two vaccine doses**

If the trial is suspended, the DSMB will review all available information (which will include the experience of all children to have been vaccinated) and make a recommendation to the study sponsor (GSK Biologicals) whether to recommence the trial

and proceed to the next sequential vaccine dose, or to stop the trial permanently. In the event that the DSMB recommend to stop the trial permanently, the FDA will be informed by GSK Biologicals that the trial is suspended.

Although the trial may be suspended by the DSMB, the LSM or the Principal Investigator, it is the responsibility of the sponsor (GSK Biologicals) to make the recommendation whether or not the trial should be stopped permanently.

In the event that the trial is suspended on the recommendation of the DSMB the sponsor (GSK Biologicals) will evaluate the information. If the sponsor concurs with the DSMB's recommendation to suspend the trial, GSK Biologicals will inform the FDA that the trial has been stopped permanently. If the sponsor's recommendation is to continue, then a report will be submitted to the FDA detailing the rationale used in reaching this decision. The agreement of the FDA will be obtained prior to restarting the trial.

## **5.2. Storage of study documentation at investigator's site**

All study documentation containing personal information relating to study subjects will be kept in a secure locked area at the investigator's site. Such documentation will only be made available to authorized personnel. All electronic data kept at the investigator's site are kept secure. Computer access is only available to authorized personnel.

## **5.3. Recruitment/Screening**

### **5.3.1. Community information**

The community in which the study will take place will be informed about the nature and design of the study. Refer to Appendix C for an overview of the recruitment plan of the study.

### **5.3.2. Screening of volunteers**

Only children with a written ICF, signed/thumb-printed and dated by parents/guardians will be screened.

Comprehension of the information contained within the ICF will be checked prior to screening by an oral interview with the volunteer's parent(s)/guardian(s). If consent is not available from both parents or guardians, the reason for the unavailability of one of the parents or guardians will be specified on the ICF form. When the parent(s)/guardian(s) of the child are illiterate, the ICF will also be signed and dated by a witness.

Subject numbers will be allocated to all volunteers who are consented for screening by their parent(s)/guardian(s). Subject numbers will be issued consecutively. Once consent is obtained, then per-protocol eligibility criteria will be checked, which will necessitate a physical examination and blood sampling for assessment of hematology, renal and liver function. This will be documented on clinic forms, which are prepared and filled in by the investigator. Each form will contain the subject number, information about the

volunteer's date of birth, household, date of screening visit, medical history, physical and laboratory screening examination. After reviewing the medical history, physical examination and laboratory results, any reasons for non-eligibility will be documented in the CRF.

The parent(s)/guardian(s) of children who have been consented for the study and found to be ineligible will receive a full explanation by a study clinician. Any clinically relevant finding will be treated appropriately by a physician. Where necessary the child will be referred to a specialist at Centre Hospitalier de Libreville for evaluation and treatment as described in Section 5.8. An overview of the laboratory assays can be found in Appendix D and further details can be found in HAS SOPs.

A study identification card will be prepared for the parent(s)/guardian(s) of each screened subject. At screening a photograph of each screened subject being held by their parent(s)/guardian(s) will be taken and attached to the study identification card. This card will also bear the name of the study to which the child is enrolled, and the child's subject number.

#### **5.4. Vaccination process**

The vaccines RTS,S/AS02D and RTS,S/AS01E will be packaged in identical boxes and will be identified by a treatment number. The unique treatment number will identify all doses of these vaccines administered to each subject. After randomization the treatment number assigns the subject to one group or another in a blinded way. Each subject will retain the same treatment number for their subsequent vaccine doses. The treatment number will be recorded on the subject's Clinic Form after the vaccine has been administered; information from the Clinic Form is subsequently transferred to the Case Report Form. The Clinic Form and Case Report Form link the subject number and the treatment number.

All vaccines will be administered by the intramuscular route to the left deltoid. Subjects who receive their vaccination in the incorrect arm will continue to receive subsequent blinded vaccinations as normal. The fact that the vaccine was administered in the wrong arm will be documented.

Vaccinations will take place at the HAS MRU or the outpatient clinic of HAS. All vaccinations will be given by a qualified person; a nurse or a doctor. A staff member experienced in the resuscitation of children will be available at all vaccination sessions. Facilities and equipment will be available to give emergency treatment in the case of an anaphylactic reaction following administration of vaccines. All children will be observed for an hour after the administration of vaccine to evaluate and treat any acute adverse events.

The process for each vaccination is as follows. The identity of the child will be confirmed using the study identification card. The subject number on this card will be cross-checked with that on the subject's clinic form, ensuring that the subject number on the clinic form matches that of the study identification card. On the day of the first vaccination the contraindications to vaccination, inclusion/exclusion criteria and ICF will be checked prior to vaccination. On the days of the subsequent vaccinations, elimination criteria and

contraindications to vaccination will be checked prior to vaccination. A vaccine clinic form will be initiated, which will give the child's identifiers, subject number and treatment number assigned after the administration of the vaccine.

Vaccines will be administered in a blinded fashion. For each vaccination during the course of the study, the Vaccine Preparer will prepare the vaccine and the Vaccinator administer the vaccine for a specific subject. Since the vaccines used in this study are of distinct appearance, the Vaccine Preparers are not blinded and together with the Vaccinators perform no other function in the study (refer to Section 6.5). The Vaccine Preparer will select the sealed box labeled with the subject's treatment number, containing the vials numbered with the treatment number, remove the vaccine vials and fill a syringe according to this study protocol (refer to Section 6.2). The Vaccine Preparer will then place a numbered opaque label with the subject's treatment number on the syringe. The purpose of masking the syringe is to blind the parent(s) or guardians(s) of the subject. The Vaccine Preparer will then pass the syringe to the Vaccinator in an adjacent room who will administer the vaccination. After administering the vaccination to the subject the Vaccinator will enter the treatment number administered to the subject on the clinic form.

Subjects who cannot be vaccinated on the originally scheduled date (see Section 4.9.1) will be vaccinated within 7 days and undergo all study procedures for the visit on the same day as vaccination. In the particular case of any child found to be febrile (axillary temperature  $\geq 37.5^{\circ}\text{C}$ ), a blood slide will be taken to investigate for malaria. Children will be treated as appropriate for their condition and will be followed up until resolution of any symptoms and be vaccinated if their clinical symptoms resolve within 7 days.

Those who cannot be re-vaccinated within 7 days of their scheduled date will continue all study procedures apart from receiving further study vaccinations.

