| STUDY CONCLUSION                                                     |                |                    |                |                |                |                |                |                |                |                    |                |

#: Field Worker visit code numbers not necessarily sequential. ● is used to indicate a study procedure that requires documentation in the individual CRF and ○ is used to indicate a study procedure that does not require documentation in the individual CRF.

a: includes analysis of hemoglobin, total white cell count and platelets

b: SAEs related to study procedures will be collected

c: all medications required by protocol to be recorded at these visits

d: record administration of immunosuppressants or other immune-modifying drugs during this period (for corticosteroids this means prednisone or equivalent,  $\geq 0.5$  mg/kg/day. Inhaled or topical steroids are allowed and should not be recorded. ALSO all immunoglobulins and blood products should be recorded during this period.

It is the investigator's responsibility to ensure that the intervals between visits/contacts are strictly followed. These intervals determine each subject's evaluability in the according to protocol analyses (see Sections 4.6 to 4.9 and Section 10.6 for details of criteria for evaluability and cohorts to be analyzed). The intervals are tabulated in Table 4.

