**Table 4 Intervals between study stages/visits**

| Interval          | Length of interval      |
|-------------------|-------------------------|
| (Visit 1→Visit 2) | Screening –28 to Day –0 |
| (Visit 2→Visit 4) | 21 to 35 days           |
| (Visit 4→Visit 5) | 21 to 35 days           |
| (Visit 2→Visit 7) | 14 months ± 1 month     |

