**Clinic Visit 4: Vaccination 2**

Day 30

- Check study identification card of vaccinee
- Check contraindications to vaccination
- Check elimination criteria
- Record unsolicited adverse events experienced by the vaccinee since the last visit
- Record pre-vaccination body temperature
- Administer the second dose of RTS,S/AS01E or RTS,S/AS02D intramuscularly in the left deltoid

Each child will be assessed for at least 60 minutes after vaccination to evaluate and treat any acute adverse events.

- Record any post-vaccination solicited symptoms
- Record any post-vaccination unsolicited adverse events
- Record any post-vaccination SAEs
- Record concomitant medication

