**Clinic Visit 5: Vaccination 3**

Day 60

- Check study identification card of vaccinee
- Check contraindications to vaccination
- Check elimination criteria
- Record unsolicited adverse events experienced by the vaccinee since the last visit
- Record pre-vaccination body temperature
- Administer the third dose of RTS,S/AS01E or RTS,S/AS02D intramuscularly in the left deltoid

Each child will be assessed for at least 60 minutes after vaccination to evaluate and treat any acute adverse events.

- Record any post-vaccination solicited symptoms
- Record any post-vaccination unsolicited adverse events
- Record any post-vaccination SAEs
- Record concomitant medication
- Blood sample to collect 5 mL blood for analysis of:
  - serology (antibodies to CS, HBs)
  - cell-mediated immunity and B-cell memory

---

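### With doses booked on the nominal Day 30 and Day 60, a 6- or 7-day deferral under Section 5.4 can give an interval of 36 to 37 days, past the 35-day Table 4 limit that decides ATP evaluability

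*Protocol*

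**What the plan says.** Section 5.4 of the protocol sets the rule for a child who is unfit for a dose on the day: "Subjects who cannot be vaccinated on the originally scheduled date (see Section 4.9.1) will be vaccinated within 7 days". Vaccination stops only after that allowance has run out: "Those who cannot be re-vaccinated within 7 days of their scheduled date will continue all study procedures apart from receiving further study vaccinations".

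Section 5.11 sets the dose visits under the headings "Clinic Visit 4: Vaccination 2", at Day 30, and "Clinic Visit 5: Vaccination 3", at Day 60. Table 3 gives the same days.

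Table 4 in Section 5.10 limits both dose intervals: "Visit 2→Visit 4) | 21 to 35 days" and "Visit 4→Visit 5) | 21 to 35 days". The text just before Table 4 gives these limits two roles. One concerns conduct: "It is the investigator's responsibility to ensure that the intervals between visits/contacts are strictly followed". The other concerns analysis: "These intervals determine each subject's evaluability in the according to protocol analyses".

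Section 4.9.1, which Section 5.4 cites, allows a deferred dose within the protocol's time window but does not say which window it means. Section 10.6.3 admits to the ATP immunogenicity cohort children who complied with protocol procedures. Section 10.8.1.1 uses that cohort for the primary anti-CS non-inferiority analysis.

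**The concern.** A deferral rule and an interval rule that apply to the same dose should agree at their outer edge, and here they do not. Section 5.4 tells the site to vaccinate a recovered child up to 7 days late. Section 5.10 makes the site responsible for keeping to a limit that, on the nominal schedule, is reached after 5 days. On deferral days 6 and 7 the investigator cannot satisfy both.

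What is at stake is membership of the primary analysis cohort. A child who was febrile at a dose visit, recovered, and was then dosed exactly as Section 5.4 directs can be lost from the ATP immunogenicity cohort. Such deferrals are foreseeable. Section 4.9.1 defers for an axillary temperature of 37.5°C or more, Section 4.3 describes intense malaria transmission, and Section 5.4 has its own procedure for children found febrile.

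**Working it through.** **Inputs (all from the protocol)**

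- Nominal dose days: 0, 30 and 60 (Table 3, Section 5.11).
- Deferral allowance: up to 7 days after the booked date (Section 5.4).
- Permitted interval, Visit 2 to 4 and Visit 4 to 5: 21 to 35 days (Table 4).
- Enrolment of 90 per group for 75 evaluable per group (Sections 4.5 and 10.5).
- Log standard deviation 0.9, margin 3.0, alpha 0.025, power 90% (Section 10.5).

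**Where the Table 4 window fits.** 28 − 7 = 21 and 28 + 7 = 35. The window is exactly 28 ± 7 days, so a 7-day deferral fits a four-week booking. The visits are set 30 days apart, and those 2 extra days are the overrun.

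**Single deferral.** Let s be the days from the previous dose to the booked date and d the deferral in days. The interval is s + d, and it breaks Table 4 if s + d > 35.

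| Booked at s | Longest interval, s + 7 | Deferral days that breach |
|---|---|---|
| 28 or earlier | 35 or less | none |
| 29 | 36 | 7 |
| 30 (nominal) | 37 | 6 and 7 |

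At s = 30, deferrals of 1 to 5 days give 31 to 35 days, all inside the window. Deferrals of 6 and 7 days give 36 and 37 days, both outside.

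**Dose 3 when Dose 2 was itself late.** If Dose 3 keeps its Day 60 booking and Doses 2 and 3 are deferred by d2 and d3 days, the Dose 2 to Dose 3 interval is (60 + d3) − (30 + d2) = 30 + d3 − d2. With d2 and d3 each from 0 to 7, this runs from 23 to 37. It exceeds 35 in three cases only:

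- d2 = 0, d3 = 6: 36 days
- d2 = 0, d3 = 7: 37 days
- d2 = 1, d3 = 7: 36 days

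**Does it threaten power?** The plan's sample size comes first. With log10(3) = 0.477 and SE = 0.9 × √(2/75) = 0.147, the ratio is 0.477/0.147 = 3.25. Then 3.25 − 1.96 = 1.29, and Φ(1.29) = 0.901, which matches the stated 90% at 75 per group. (Reading the stated SD as log10 is what reproduces it.) With the noncentral t and a true ratio of 1, power is:

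| Evaluable per arm | Power |
|---|---|
| 90 | 0.943 |
| 85 | 0.930 |
| 80 | 0.915 |
| 75 | 0.897 |

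The 75 is already net of losses: 90 − 75 = 15 per arm are allowed for. Losing 5 of 90, an assumed figure, would leave 0.930.

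**Check of the fix.** With a 37-day limit, a dose booked at s ≤ 30 never breaches (30 + 7 = 37), and the 23-to-37 range for Dose 3 lies inside 21 to 37. A dose booked at s = 31 could still reach 38 days, so the deferral rule also has to name the window.

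**The case against.** The strongest reply is that the two windows do different jobs. Section 5.4 decides whether a child still receives the vaccine, Table 4 decides who is analysed per protocol, and a dosing window wider than the ATP window is ordinary practice. Much of this stands. In particular, a reader might infer that ATP membership of a child dosed at day 36 or 37 is undefined, because that child has complied with Section 5.4. The documents do not support that, since Section 5.10 says the Table 4 intervals decide evaluability. The reply does not dispose of the conduct instruction, however. Section 5.10 also makes strict adherence to the intervals the investigator's duty, and on deferral days 6 and 7 that cannot be squared with Section 5.4.

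A second reply is that the limits can be read as cumulative: no more than 7 days late and no more than 35 days after the last dose, with Section 4.9.1 supplying the link. That reading is possible, but Section 4.9.1 does not name Table 4. Section 5.4 cites Section 4.9.1 and supplies 7 days, which can equally be the window meant. A cross-reference at 35 days would remove the contradiction, but at a cost: a child fit again only on deferral day 6 or 7 would then go undosed and would still be outside the ATP cohort.

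A third reply is that a site can book at four weeks and never meet the problem. That is correct, and it limits the point to bookings later than 28 days. The protocol's own stated days are nevertheless 30 and 60.

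**Conclusion.** The inconsistency is real and minor. It rests on booking at the nominal Day 30 and Day 60 (or any day after day 28) and on a deferral long enough to pass day 35. At the nominal spacing the overrun is 1 or 2 days, on deferral days 6 and 7 only. For Dose 3 it also needs Dose 2 to have been on time, or 1 day late with a 7-day deferral of Dose 3.

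The number of children affected cannot be derived, because the protocol gives no deferral rate. Two larger conclusions are tempting and should not be drawn:

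- **A power shortfall.** Taking losses off the 75 evaluable per arm would suggest one, but 15 per arm are already allowed for. Nothing in the protocol indicates that these few cases would come on top of a fully used allowance.
- **Bias in the GMT ratio.** None is shown. Both arms follow the same schedule, those assessing the endpoints are blinded, and Section 10.8.1.1 adds a Total Vaccinated Cohort analysis if more than 5% of subjects are excluded.

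What remains is that following one section exactly can put a child outside the primary analysis cohort, and that is avoidable.

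**What to change.** In Table 4, raise the upper limit for Visit 2 to Visit 4 and for Visit 4 to Visit 5 from 35 to 37 days. In Sections 4.9.1 and 5.4, name the Table 4 window as the limit for any deferred dose, so that a dose booked later than 30 days after the previous one cannot pass 37 days by using the full 7-day deferral.

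This changes two table cells and one phrase in each of two sections. The downside is an ATP dosing interval up to 2 days wider, equally in both arms.

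Booking doses at 28 days would be an equivalent alternative: 28 + 7 = 35 keeps every permitted deferral inside the present Table 4 limits.

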## **5.5. Home follow-up visits for assessment of reactogenicity (7-day follow-up period)**

Trained field workers under the supervision of the Principal Investigator will visit each enrolled child at daily intervals for Days 1 to 5 post Dose 1; a study clinician will examine the child in the clinic on Day 6. For all other doses, the field workers will visit each enrolled child at daily intervals for Days 1 to 6 post each vaccination (see below in detailed study procedure; Section 5.11). In the event that the field worker finds any Grade 3 solicited general or unsolicited symptoms, the volunteer will be brought to HAS for examination by a study clinician. Any further clinical data, including treatment provided, will be written on diary cards and HAS clinic forms and transcribed onto the CRF. If the physician finds that the volunteer has experienced an SAE the appropriate measures will be taken to report this (See Section 8.7).

Diary cards will be checked and verified by the Principal Investigator or designate before transcription onto CRFs after the 7-day follow-up. The Principal Investigator has a primary responsibility for the data transcribed onto the CRFs. Unresolved AEs will be followed-up according to the instructions in Section 8.6 by field workers under the

supervision of the Principal Investigator and data will be entered onto the CRF. The procedures and frequency of visits will be outlined in a SOP at the investigator's site.

Analgesics/antipyretics will be provided to field workers for the treatment of children with injection site pain and fever and their use will be documented. Parent(s)/guardian(s) will not routinely be provided with these medications.

## **5.6. Monitoring of hematological and biochemical laboratory parameters**

Blood for safety monitoring of hematology, renal and hepatic function will be measured at screening, one week post Dose 1, one month post Dose 3 and 12 months post Dose 3. The hematological and biochemical parameters will be documented on the CRF. For all values outside the normal range (refer to Table 10), the reason and/or clinical condition will be documented. Results of hematological and biochemical laboratory tests will be reviewed as soon as they are generated. Any value outside the normal range will be managed as appropriate by a medically qualified individual under the supervision of the Principal Investigator (refer to Section 8.6). Guidance on when to report abnormalities as SAEs is given in Section 8.3.

## **5.7. Surveillance for SAEs (all subjects)**

### **5.7.1. At health facilities**

Morbidity surveillance will be in place for this trial. The HAS will be the source of primary outpatient and inpatient care for the study participants. The surveillance system will provide a comprehensive recording of all outpatient attendances, the investigational results, diagnosis and management. Prior to the start of the study, all parent(s)/guardian(s) of volunteers will be educated on the appropriate action they should take if their child becomes unwell at any time during the study period. They will be asked not to medicate their child at home, but to seek medical care at the HAS.

A physician will be available 24 hours per day at HAS to receive and identify study participants when they present and to ensure complete investigation and documentation of the attendance.

All children attending as outpatients within the age range of the trial will be asked if the child is in this study and to provide the child's vaccine study identity card (see Section 5.3.2 for details of identity cards). If the identity cards are not available, the identity of the child will be confirmed against details collected at enrollment to the trial.

The child will be fully assessed by an appropriately qualified physician. This information will be recorded on a HAS clinic form. This form will provide a record of the child's name and study number, key symptoms and signs, axillary temperature, results of the laboratory tests and imaging examinations available at the time of form completion, the diagnosis, the treatment prescribed and will state whether hospital admission was required.

These forms will be retained by the study personnel in the HAS MRU Outpatient Department until they are sent to the HAS MRU data unit at the end of each working day. At the HAS MRU data unit, the questionnaires will be reviewed by the Principal Investigator or delegate. If it is necessary to report any of these consultations as a serious adverse event, the Principal Investigator or delegate will review the child as necessary and complete an SAE form to report the event (as specified in Section 8.5).

Children requiring inpatient care will be admitted to HAS, their clinical course, treatment and results of further investigations will be documented in their hospital records. The hospital records and inpatient surveillance will be the source documents for the SAE reports. When necessary, children will be followed to resolution of SAEs as outpatients.

